# *N*-acetylcysteine (NAC) in schizophrenia resistant to clozapine: a double blind randomised placebo controlled trial targeting negative symptoms

**DOI:** 10.1186/s12888-016-1030-3

**Published:** 2016-09-15

**Keywords:** *N*-Acetylcysteine, Clozapine, Schizophrenia, Negative Symptoms, Cognition, Biomarkers

## Abstract

**Background:**

Clozapine is an effective treatment for a proportion of people with schizophrenia (SZ) who are resistant to the beneficial effects of other antipsychotic drugs. However, anything from 40–60 % of people on clozapine experience residual symptoms even on adequate doses of the medication, and thus could be considered ‘clozapine resistant’. Agents that could work alongside clozapine to improve efficacy whilst not increasing the adverse effect burden are both desired and necessary to improve the lives of individuals with clozapine-resistant SZ. *N*-Acetylcysteine (NAC) is one such possible agent. Previous research from our research group provided promising pilot data suggesting the efficacy of NAC in this patient population. The aim of the study reported here is to expand this work by conducting a large scale clinical trial of NAC in the treatment of clozapine-resistant SZ.

**Methods:**

This study is an investigator initiated, multi-site, randomised, placebo-controlled trial. It aims to include 168 patients with clozapine-resistant SZ, divided into an intervention group (NAC) and a control group (placebo). Participants in the intervention group will receive 2 g daily of NAC. The primary outcome measures will be the negative symptom scores of the Positive and Negative Syndrome Scale (PANSS). Secondary outcome measures will include: changes in quality of life (QoL) as measured by the Lancashire Quality of Life Profile (LQoLP) and cognitive functioning as measured by the total score on the MATRICS. Additionally we will examine peripheral and cortical glutathione (GSH) concentrations as process outcomes.

**Discussion:**

This large scale clinical trial will investigate the efficacy of NAC as an adjunctive medication to clozapine. This trial, if successful, will establish a cheap, safe and easy-to-use agent (NAC) as a ‘go to’ adjunct in patients that are only partly responsive to clozapine.

**Trial registration:**

Australian and New Zealand Clinical Trials Registration Number: Current Randomised Controlled Trial ACTRN12615001273572. The date of registration 23 November 2015.

## Background

### Schizophrenia

Schizophrenia (SZ) is a severe and enduring mental illness, afflicting 1 % of the population. Despite some treatment advances, most notably the discovery of the antipsychotic drugs, many people with SZ continue to suffer substantial disability associated with ongoing distressing symptoms. For example, in Australia (where this trial will take place) the recent Survey of High Impact Psychosis (SHIP) found that 41.3 % of the 1825 participants with a psychotic illness were, despite treatment, experiencing persistent psychotic symptoms [1]. Negative symptoms and cognitive deficits are the most poorly responsive to pharmacological interventions, yet carry the greatest disability in terms of poorer overall personal, social and occupational functioning.

### Clozapine

Clozapine is the most effective antipsychotic drug for treatment–resistant SZ. Due to the significant adverse event profile, it is generally only prescribed to those who have not responded to other antipsychotics and is often considered a ‘last resort’. Clozapine is recommended in all major treatment algorithms for treatment resistant SZ. It is commonly prescribed in Australia, with 22 % of the SHIP sample being on this agent. However, a substantial proportion of people with SZ do not respond adequately to clozapine, with 40–60 % having residual negative and cognitive symptoms despite an adequate trial of clozapine [2] or due intolerable side effects which limit the option of increasing clozapine dose. Attempts to enhance the therapeutic efficacy of clozapine have met with mixed success. A recent review by the [name] (Chief Investigator of this study) outlined a range of augmentation strategies that have been investigated in people who ‘failed’ clozapine. These include other antipsychotics, antidepressants, mood stabilisers, and glutamatergic agents, and although some showed benefits for a proportion of patients, strategies that have been encouraging in small case series have mostly not been confirmed in subsequent more rigorous studies [3]. Agents that could work alongside clozapine to improve efficacy whilst not increasing the side effect burden are essential if we are to improve to lives of clozapine-resistant SZ patients. One such potential agent is *N*-acetylcysteine (NAC), a glutathione (GSH) precursor.

### *N*-Acetylcysteine (NAC)

NAC has been shown to modulate a number of processes involved in psychiatric disorders including neuroinflammation, oxidative stress, and the regulation of glutamate and dopamine neurotransmitter systems. NAC has been trialled as an augmenting agent for a range of disorders including addiction (smoking, cocaine, cannabis and gambling for example), autism, Alzheimer’s, attention deficit hyperactivity disorder (ADHD), and impulse control disorders (nail biting, skin picking, trichotillomania) to name a few [4]. While more high quality trials are needed to confirm the efficacy of NAC in these disorders, at this stage the results are promising.

The study described here is born out of a previous randomised controlled trial of NAC as an adjunctive therapy for SZ specifically [5]. Investigators for this previous trial assessed the efficacy of NAC as an adjunct to treatment as usual in people with SZ; of the 140 enrolled participants, 45 % were on clozapine. Overall, results showed significant improvements on the Clinical Global Impression-Severity Scale (CGI-S; *d* = 0.43; *p* < 0.05) and Positive and Negative Syndrome Scale (PANSS), negative (*d* = 0.52; *p* < 0.05) and general (*d* = 0.46; *p* < 0.05) subscales. NAC was extremely well tolerated with no significant adverse events reported in the NAC group. Additionally, abnormal involuntary movements (a side effect of antipsychotic medication) were reduced during NAC treatment. Secondary analyses using the clozapine patients only [6], showed these benefits were robust for the clozapine patient group. That is, there were significant reductions in PANSS negative scores from baseline to endpoint in the NAC group. Adjusting for baseline score using least square means, the difference between the placebo (*n* = 24) and NAC (*n* = 25) groups was statistically significant (Mdiff = 3.87, SE = 1.84, 95 % CI [0.14, 7.59], *p* < 0.05, d = 0.61). Importantly, Farokhnia et al. [7], in an independent study, also demonstrated similar improvements for NAC for negative symptoms of SZ (as an adjunct to risperidone). Given these findings, and the lack of studies to date that have specifically targeted those prescribed clozapine, the current trial is timely and warranted. Furthermore, the pilot work clearly indicates the feasibility of the trial design.

### Quality of life

A review of the literature shows that people diagnosed with SZ report a lower quality of life (QoL) than the general population [8, 9]. Contributing factors include psychotic symptoms [10], as well as depression and anxiety [11]. Neurocognition has also been linked to QoL with greater cognitive functioning linked to higher objective but lower subjective QoL [12]. Finally, insight has actually been shown to reduce subjective QoL [13].

### Cognition

Cognitive impairment is common in SZ and is thought to play a role in non-response to drug treatment. Indeed, a recent study by de Bartolomeis et al. [14] established that people with treatment resistant SZ had significantly poorer verbal memory and executive function than responders. Additionally, severity of global cognitive impairment was significantly correlated with negative symptom severity in this treatment resistant cohort. There is now substantial evidence from animal studies that NAC improves cognitive function [15], more specifically attention, executive function and memory. There has been very little investigation of the impact of NAC on cognition in human studies. Some early evidence indicates that it may improve specific areas of cognition including memory [16]. Besides being associated with treatment response, cognitive impairment is also associated with poorer social and occupational outcome [17]. Research suggests that improvements in cognition (through cognitive remediation for example) are associated with improvements in these areas [18]. Thus, in the proposed study, we will investigate neurocognitive changes as a secondary outcome measure. We will include premorbid IQ, current IQ and general cognition as examined using the MATRICS, which is considered the gold-standard cognitive assessment in clinical trials for patients with SZ [19].

### Biological mechanisms

Our study has also been designed to enable a novel investigation of the biological effects of NAC treatment. This includes the measurement of peripheral markers including thiols (such as GSH, cysteine, cysteinyl-glycine, NAC) and corresponding disulphides (such as glutathione disulphide (GSSG) and cystine). These analyses will be used to track longitudinal changes in GSH and related compounds through the course of the proposed trial. In addition to peripheral GSH, we will measure cortical GSH via proton magnetic spectroscopy (MRS). Recently there have been substantial developments in both the field strength and spectral acquisition of MRS which now permits the accurate measurement of GSH in the human brain *in vivo*. For example, Do et al. [20] demonstrated that GSH is reduced in the cortex of SZ patients using MRS. Therefore, we will use *in vivo* MRS to assess changes in cortical GSH levels in a subset of participants in the proposed study. This will be completed by obtaining the concentration levels of GSH in the medial prefrontal cortex [21]. The longitudinal changes of these concentrations will be mapped at three time periods across the proposed study: between baseline and 8 weeks to examine for rapid changes; and then at 52 weeks to assess long-term change. Concentrations of GSH across the three time periods will be used in our group-based analyses. The collection of both peripheral and cortical data will allow a full characterisation of the effects of NAC on GSH by exploring links between blood and MRS GSH levels.

### Research aims

This project seeks to expand our existing work by conducting a multi-site randomised placebo-controlled trial of NAC in the treatment of clozapine-resistant SZ, with 8, 24 and 52 week assessments. We will target negative symptoms (primary outcome), quality of life and cognition (secondary outcomes). An additional novel aspect of this proposed study is the examination of both peripheral and cortical GSH concentrations, the latter in a subset of patients using MRS. This will be the first study using NAC to target drug resistant clozapine treated SZ patients specifically; and the first to conduct a 52-week outcome study of the efficacy of NAC in SZ. It is hypothesised that NAC will be superior to placebo in the treatment of negative symptoms in SZ patients currently taking clozapine. Additional benefits are predicted in their quality of life and cognitive functioning. Further analysis of peripheral and cortical GSH concentrations is expected to show increases, whereby increases in cortical GSH will increase cortical functioning.

## Methods

### Study design and plan

The study is a phase IV, multi-site, 2-arm, 52-week, randomised, double-blind, placebo-controlled trial of 2 g of NAC per day (taken as two 500 mg capsules twice per day or matching placebo), in 168 participants diagnosed with SZ (see Fig. 1 for study outline). In addition to baseline assessments, follow-ups will take place at 8, 24 and 52 weeks (see Table 1 for a list of study assessments). A subsample at the Melbourne site will be invited to undergo a brain scan using MRI (*N* = 42). Scans will be performed at baseline, 8 and 52 weeks. The study protocol was approved by the St Vincent’s Hospital Human Research Ethics Committee (HREC-A HREC-D 030/16), this committee has jurisdiction over all the participating sites. An executive steering committee (all authors) oversees project planning, conduct and ongoing data collation.

**Fig. 1 Fig1:**
[figure not shown]
Study Outline

**Table 1 Tab1:** Study Assessments and Timeline

		0 week	2, 4 & 6 w	8 weeks	24 weeks	52 weeks
General	Demographic questionnaire	X		X^1^	X^3^	X^3^
Diagnosis	MINI	X				
Symptoms	Interview to rate PANSS and CAINS	X		X	X	X
	Calgary depression scale for schizophrenia (CDSS) combined with the Montgomery Asberg Depression Scale (MADRS)	X		X	X	X
Safety	Adverse symptoms checklist (SAFTEE)	X	X^2^	X	X	X
	ECG	X				X
	Blood test for clozapine monitoring	X		X	X	X
QoL	Manchester Quality of Life Scale (MANSA)	X		X	X	X
	Assessment of Quality of Life (AQoL)	X		X	X	X
Cognition	The Wechsler test of adult reading (WTAR): Premorbid IQ	X				
	Wechsler abbreviated scale of IQ (WASI): Current IQ	X		X	X	X
	MATRICS	X		X	X	X
Biomarkers	Blood sample for biomarkers	X		X	X	X
Neuro-imaging^3^	Magnetic resonance spectroscopy (MRS)	X		X		X

^1^Shortened version to note for changes in work, study, living arrangements

^2^Telephone safety check

^3^Only participants who are in the Melbourne arm and provide informed consent for the imaging component will be administered these additional assessments

### Setting

The study will be co-ordinated from the Mental Health Department of St Vincent’s Hospital, a large metropolitan teaching hospital in Melbourne, Australia. The study will be conducted across four Australian sites: Melbourne (St Vincent’s Mental Health Service), Sydney (Cumberland Hospital), Adelaide (Northern Adelaide Local Health Network), and Brisbane (Metro South Addiction and Mental Health Service).

### Participants

Forty-two patients will be recruited from each of the sites, with a total target of 168 participants aged 18–65 years meeting DSM-5 criteria for SZ. Investigators at each site will be responsible for recruiting participants through advertising and engagement with clozapine clinics associated with their site. As we are interested in clozapine patients who have residual symptoms, all potential participants will be screened and assessed for eligibility. The following inclusion criteria are to be adhered to: (1) Aged 18–65 years; (2) Confirmed diagnosis of SZ via clinical interview; (3) Have been on clozapine at an adequate dose for at least 6 months, ascertained by a current serum level of >350 mcg/L and with residual symptoms (see 4.)^1^; (4) Have a PANSS score of ≥60 or at least two negative symptom items of >4^2^; (5) Have the capacity to provide consent to the study; and (6) Be utilising effective contraception (i.e., oral or barrier contraception) if female and of childbearing age. In addition, the following exclusion criteria will be applied: (1) Participants who are currently taking NAC; (2) Participants who are allergic to NAC or any component of the preparation; (3) Participants who are currently prescribed nitro-glycerine (significant potential interaction with NAC); (4) Participants who have diabetes mellitus and on insulin replacement (including exenatide) (moderate interaction); (5) Participants taking Aralen (moderate interaction); (6) Participants who regularly take >200 mg/day selenium (moderate interaction); (7) Participants who regularly take anticoagulants (moderate interaction) (excluding aspirin and non-steroidal anti-inflammatories); (8) Change in medication from clozapine to another antipsychotic; (9) Participants with known primary or secondary autoimmune disorders; (10) Recent gastrointestinal ulcers; (11) Recent renal stones; and (12) Females who are pregnant or lactating.

Power was calculated to detect a medium effect size of *d* = 0.5 as described in an earlier NAC and SZ paper [5] and the calculations followed the method described by Diggle et al. [23]. These calculations assumed one primary outcome measure (PANSS Negative scores), four assessment points (baseline, 8-weeks, 24-weeks, and 52-weeks follow-ups), a study-wide Type I error rate (α) of 0.01, a Type II error rate (β) of 0.10 (power of 0.90), a correlation of post-treatment scores with baseline measurements (ρ) of 0.70, employing a two-tailed statistical test. To detect the effect size of *d* = 0.5, 45 participants in each of the control and intervention groups will be required. Allowing for up to 46 % attrition (based on a 20 % dropout over the first 8 weeks and a further 30 % dropout over the ensuing 44 weeks), a total of 168 participants, or 84 in each group will be recruited. Similar attrition rates are reported in other treatment trials with treatment resistant SZ. To accommodate the required number of patients, at least 42 will need to be recruited from each of the four study sites. For the MRS component, groups of 15–20 are widely accepted as an appropriate size to permit appropriate neuroimaging analysis. As noted earlier the anticipated numbers, including drop out and ineligibility for the MRS component are 40 at baseline, 36 at 8-weeks and 52-weeks. Thus, the current study will be adequately powered for the MRS component.

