### Safety

The Adverse Symptom Checklist (known as SAFTEE) is a 21-item scale that rates the presence and severity (0 = not present to 3 = severe) of common symptoms associated with psychotropic treatments. As well as being assessed at baseline, 8, 24 and 52 weeks, a telephone assessment at 2, 4 and 6 weeks will also be completed using this assessment. Clozapine levels will be measured at baseline and 8, 24 and 52 weeks to ensure adherence and to ascertain any pharmacokinetic interactions with NAC (we do not expect any such effects as the kinetics of the two agents do not suggest interaction). As well as clozapine levels, hepatic and renal function, full blood count, other metabolic information and electrocardiogram (ECG) will be performed as part of routine clozapine monitoring will be maintained according to local requirements.

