### Trial status

Patient recruitment was about to commence at the time of manuscript submission. Data collection will continue until at least June 2019.

Australian and New Zealand Clinical Trials Registration Number (TRN) ACTRN12615001273572 https://www.anzctr.org.au/Trial/Registration/TrialReview.aspx?id=369601.

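### Exclusion 6 sets the selenium limit at more than 200 mg/day, which would exclude no one at any plausible supplement intake; the unit is probably wrong and should be confirmed

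*Protocol article*

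**What the plan says.** The Participants section introduces the list with "In addition, the following exclusion criteria will be applied", so these are operative criteria and not background. The sixth is "Participants who regularly take >200 mg/day selenium (moderate interaction". It appears once; no other section restates it, expresses it in micrograms or gives a source for the limit.

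Three other exclusions carry the same interaction grade: insulin-treated diabetes (4), Aralen (5) and regular anticoagulant use (7). None of them has a dose limit. The fifth, for example, is simply "Participants taking Aralen (moderate interaction".

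Inclusion criterion 3, in the same section, expresses the clozapine requirement in micrograms: "ascertained by a current serum level of >350 mcg/L".

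**The concern.** An eligibility limit is applied as written. The authors chose to screen for selenium because they regard it as interacting with NAC, and they made this exclusion depend on a daily amount. If that amount lies far above anything a participant would take, the exclusion is in the list but does nothing. Of the four exclusions with this interaction grade, only the selenium one depends on a quantity, so only it can be emptied by a wrong unit.

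Two things are at stake. First, people whom the sponsor meant to keep out could be enrolled for up to 52 weeks of NAC at 2 g/day. Second, four sites screen from this list, and one might apply the printed figure while another silently reads it as micrograms.

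**Working it through.** No sample-size, power or error-rate figure is involved. The check is a unit conversion and a comparison.

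**Inputs**
- Printed limit: 200 mg/day (Participants, exclusion 6).
- Selenium intake among supplement users: not given in the article. Assumed range 50 to 400 mcg/day, with 1,000 and 5,000 mcg/day added as extreme values to test how far the result depends on that range.

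**Step 1: convert the limit.** 200 mg × 1,000 mcg/mg = 200,000 mcg/day.

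**Step 2: divide the limit by intake.**

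| Assumed intake (mcg/day) | 200,000 ÷ intake |
|---|---|
| 50 | 4,000 |
| 100 | 2,000 |
| 200 | 1,000 |
| 400 | 500 |
| 1,000 | 200 |
| 5,000 | 40 |

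**Step 3: ask what it would take for the limit to bind.** Someone at the top of the assumed range would need more than 500 times that intake to be excluded. The range could be too low by a wide margin and the result would not change.

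**Step 4: try the alternative reading.** A limit of 200 mcg/day falls inside the assumed 50 to 400 mcg/day and would separate lower from higher users, as a screening limit should. If that was the intention, the printed figure is too high by 200,000 ÷ 200 = 1,000.

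**What cannot be computed.** The article does not say how many of the 168 participants might take selenium, so the number affected cannot be estimated.

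**The case against.** The strongest objection is that nothing in the article contradicts the figure. It appears once, with no intake data or source beside it, and it looks implausible only because of an intake range brought in from outside. This is right about where the premise comes from, and it is why the range is declared as an assumption. It does not rescue the criterion, because the gap is still 40-fold at 5,000 mcg/day and the conclusion does not turn on the exact range.

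A second objection is that the microgram unit in inclusion criterion 3 is a serum concentration, not a daily intake. It shows that the authors distinguish the two units, not that they meant micrograms for selenium. That stands: it is weak support, and 200 mcg/day remains a probable reading only.

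Third, a journal article condenses a fuller protocol that is not shown, and the screening form may already be right. That also stands. The error may be confined to the published wording, and the article cannot settle this.

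Fourth, the consequence is small. The article grades the interaction only as moderate and describes no specific harm. Adverse symptoms are rated with the SAFTEE checklist at every assessment visit whatever the selenium intake, and between baseline and week 8 "a telephone assessment at 2, 4 and 6 weeks will also be completed using this assessment". This is accepted and is reflected in the severity.

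**Conclusion.** The criterion is wrong as written, with minor severity. On the stated assumption of 50 to 400 mcg/day among supplement users, the printed limit is 500 to 4,000 times realistic intake and would exclude nobody. A unit slip is the most likely cause, but this is an inference to be confirmed and confidence in it is moderate.

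The effect is limited to eligibility and safety screening. Sample size, power, the analysis and the primary conclusion do not change, and no effect on the glutathione outcomes is claimed.

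**What to change.** Confirm the intended unit against the source from which the interaction list was drawn, then restate the limit in the protocol, most likely as more than 200 mcg/day. Check the form used at the four sites and correct it only if it carries the same figure.

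The Trial status section says "Patient recruitment was about to commence at the time of manuscript submission", so at that date the check could be made at or near the start of screening. If screening has since moved on, the selenium intake of those already enrolled should be looked at once the unit is settled.

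The cost is one check and one changed unit. The small downside is that, if micrograms were intended, a few supplement users would become ineligible.

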### Randomisation and blinding

The study procedure will follow the SPIRIT guideline [24]. The trial is a randomised, controlled, double-blinded superiority trial of two parallel patient groups. Randomisation will be performed independently of the researchers by an independent researcher and will employ block randomisation (2 × 4) with a 1:1 allocation to NAC or placebo. Allocation will be concealed from local investigators, who will assign a number to the participant that will be linked to a prescription from the associated pharmacy. All participants will be dispensed the same number of capsules each month.

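### The 46% attrition allowance does not follow from its stated dropout rates, which combine to 44% or 50%; 168 follows from the 46%, not from those rates

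*Protocol article*

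**What the plan says.** The sample-size justification is in the Participants section of the protocol article. It concludes that "45 participants in each of the control and intervention groups will be required". It then inflates that number: "Allowing for up to 46 % attrition", a figure it says is "based on a 20 % dropout over the first 8 weeks and a further 30 % dropout over the ensuing 44 weeks". The result is that "a total of 168 participants, or 84 in each group will be recruited", and the per-site quota follows: "at least 42 will need to be recruited from each of the four study sites". The Randomisation and blinding section gives a "1:1 allocation to NAC or placebo", so the equal split of 168 is consistent with the design.

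The same paragraph gives separate expected numbers for the MRS subset: 40 at baseline and 36 at both week 8 and week 52. It judges these sufficient because 15 to 20 per group is regarded as an acceptable size for imaging work.

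The text does not say whether the later 30% is a share of those remaining at week 8 or of all randomised. It gives no other source for 46% beyond a remark that other trials in treatment-resistant patients saw similar attrition.

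**The concern.** The 46% is presented as the result of two dropout rates given in the same sentence, and neither ordinary way of combining them produces it. This is a stated figure that disagrees with its own stated inputs, so it is not a detail that an article would leave to a fuller document.

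The figure matters because it is the only link between the 45 per arm that the power calculation asks for and the 168 to be recruited. The two readings fall on opposite sides of the plan's own requirement: one leaves slightly more than 45 per arm at week 52, the other slightly fewer. A reader cannot tell from the text which the investigators intended.

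The same assumption bears on the MRS subset. Its participants come from the main trial, yet their expected loss is far lower than the main-trial rates, and no reason is given.

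**Working it through.** **Inputs**, all from the Participants section: 45 required per arm; overall attrition 46%; dropout of 20% in weeks 0 to 8 and 30% in the following 44 weeks; 84 recruited per arm, 168 in total; four sites at 42 each; MRS numbers 40, 36 and 36.

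**Step 1: reproduce the plan's figure.** Recruited per arm = required / (1 − attrition) = 45 / (1 − 0.46) = 45 / 0.54 = 83.3, rounded up to 84. Total 2 × 84 = 168, and 4 × 42 = 168. The stated target is reproduced exactly from 45 and 46%.

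**Step 2: combine the stated dropout rates.**
- Sequential (30% of those remaining): 1 − 0.80 × 0.70 = 1 − 0.56 = 44%.
- Additive (30% of all randomised): 20% + 30% = 50%.

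Neither is 46%. To reach 46% sequentially after a 20% first-phase loss, the second-phase loss would have to be 1 − 0.54/0.80 = 32.5%. With the second phase held at 30%, the first would have to be 1 − 0.54/0.70 = 22.9%. Rounding to whole percentages does not close the gap: even 20.5% and 30.5% give 1 − 0.795 × 0.695 = 44.7%.

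**Step 3: carry each reading through the same inflation.**

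| Attrition | Needed per arm for 45 | Total | Left from 84 per arm |
|---|---|---|---|
| 46% (stated) | 45/0.54 = 83.3 → 84 | 168 | 84 × 0.54 = 45.4 |
| 44% (sequential) | 45/0.56 = 80.4 → 81 | 162 | 84 × 0.56 = 47.0 |
| 50% (additive) | 45/0.50 = 90 | 180 | 84 × 0.50 = 42.0 |

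**Step 4: apply the same rates to the MRS subset.** The stated numbers imply a loss of 4/40 = 10% by week 8 and none from week 8 to week 52. The main-trial rates give 40 × 0.80 = 32 at week 8. At week 52 they give 40 × 0.56 = 22.4 (sequential) or 40 × 0.50 = 20 (additive). If the subset splits evenly between arms, that is about 11 or 10 per arm, against 36/2 = 18 as stated and the 15 to 20 per group that the section relies on.

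**The case against.** The strongest reply is that the discrepancy is two percentage points in the safe direction. The allowance is worded as a ceiling; 44% lies under it and 50% does not. Dropout described as further loss in a later period also reads most naturally as loss among those still enrolled. On that reading 84 per arm leaves 47 and the requirement is met with a small margin. The over-recruitment is trivial: 162/4 = 40.5, so equal recruitment would need 41 per site, or 164 in total, four fewer than planned. All of this stands, and it is why the point is modest. It does not make 46% follow from 20% and 30%.

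Three stronger readings are tempting and are not supported.

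- *That 168 has no derivation.* It has one: 45/0.54 gives 84 per arm. Only the step from the two dropout rates to 46% is broken.
- *That 46% was worked backwards from 168.* It is true that 1 − 45/84 = 46.4%, but the forward calculation from 46% also lands on 84, so this coincidence says nothing about direction.
- *That the retained numbers can be turned into a week-52 completer power, and the trial shown to be underpowered.* The plan's calculation is a repeated-measures one with four assessment points. The Statistical analyses section specifies a mixed model over weeks 8, 24 and 52 that uses all available data, so someone lost after week 8 still contributes. A single-visit model gives only about 0.75 even at the intended 45, against the plan's 0.90, so it measures a difference of method and not this defect.

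On MRS, it can fairly be said that a separately consented subset at one site may be retained better than the trial as a whole. That is possible, but the article does not say so.

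**Conclusion.** The inconsistency is real and small. The stated dropout rates give 44% or 50%, not 46%, and would lead to 162 or 180 participants instead of 168. On the sequential reading, which is the more natural one and fits the ceiling, the target is slightly conservative, with about 47 per arm retained against 45 required. The shortfall to 42 per arm arises only if the 30% is a share of all randomised, a reading that exceeds the plan's own ceiling. A reader might infer that the trial is under-recruited; the document does not support that as the main conclusion.

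These results take 45 per arm as given and treat dropout as equal in the two arms. The MRS figures also assume that main-trial dropout applies to the subset and that it splits evenly between arms. Under those assumptions the week-52 imaging groups would be about 10 or 11 each, below the size the plan calls adequate. This shows that the two retention assumptions need reconciling; it does not show that the MRS figure is wrong.

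**What to change.** Keep 168 and correct the sentence so that the overall figure matches its basis. Use one of two versions:

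- 20% lost by week 8 and 30% of those remaining lost by week 52, 44% overall, with about 47 per arm retained at week 52 from 84; or
- 20% and then 30% of all randomised, 50% overall, with 42 per arm retained. In this case restate the power with the plan's own repeated-measures method, since 42 is below the 45 it requires.

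In the same paragraph, either bring the expected MRS numbers at weeks 8 and 52 into line with the chosen dropout assumption or give the reason for expecting better retention in that subset. If they are brought into line, revisit the statement that the component is adequately powered.

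The cost is one corrected sentence and one added sentence, plus a power recalculation only if the additive reading was meant. No extra patients and no change to the design are needed.
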